### Care as usual

Regular healthcare, unrelated to the WHS program, is considered care as usual. Programs already running within the company are also considered CAU.

### Outcomes

#### Effect evaluation

The primary outcomes in this study are work ability, productivity and absenteeism.

– Work ability is measured with the Work Ability Index (WAI) [13]. The WAI consists of 28 questions focusing on mental and physical work ability, injuries and diseases, and future expectations. A sum score is calculated, ranging from 7–49.

– Productivity at the individual level is measured by self-report using the Quality and Quantity (QQ) questionnaire [39]. The QQ addresses the quality and quantity of work during the previous workday with two questions, each to be answered with an 11-point Numeric Rating Scale (NRS).

– Absenteeism data are provided by the occupational health service (OHS).

The secondary outcomes are psychosocial and physical workload, health status, and vitality.

– Several aspects of the psychosocial workload are measured by the second version of the Copenhagen Psychosocial Questionnaire (COPSOQ II) [40]. These aspects are quantitative work demands, work pace, autonomy, possibilities for development, meaning of work, job satisfaction, social support from supervisor, social support from colleagues, social relationships among colleagues, and sense of community. This set of concepts comprises 19 items. Reproducibility of the Dutch language version of the COPSOQ has been shown to be adequate to good [41].

– Self-reported health status is evaluated by the Dutch version of the EuroQol-5D [42]. It consists of five short questions on various health domains (e.g. mobility) and a health thermometer (0–100). The valuation of EQ-5D scores is based on the Dutch tariff, and results in scores between 0 (dead) and 1 (completely healthy).

– Self-reported vitality is assessed by a subscale of the RAND-36 questionnaire [43]. This scale consists of four questions on a 5-point Likert scale. The RAND-36 is a highly reliable instrument with satisfactory construct validity [44].

#### Covariates

Personal and work characteristics are assessed as covariate in this study.

– Most personal and work characteristics (e.g. age, gender, commuting time) are obtained through the questionnaire. Additional personal and work characteristics (e.g. contract hours, function years) are retrieved from the company headquarters.

– To assess physical workload, movement, and posture during work, a short version of the Dutch Musculoskeletal Questionnaire (DMQ) is administered [45]. The 21 items of the DMQ focus on repetitive movement, awkward postures, and force components. Validity has been shown to be sufficient [45].

#### Cost-benefit evaluation

The cost-benefit of the POSE program will be evaluated from the employers’ perspective. The cost-benefit analysis will evaluate the total costs of the POSE program for the company and will compare absenteeism costs before and after the POSE program. Costs (in Euros) include:

– Costs of the POSE program, which are the costs of the program itself and the sequential costs of company interventions (excluding insured interventions).

– Costs due to time spent by employees on the different elements of the POSE program (questionnaire, assessments, counselling, interventions), which results in lost productivity.

– Absenteeism costs. These data are obtained from the OHS’s registry system. The number of absence days will be expressed in monetary terms.

– Productivity loss at work which will be assessed using the quantity scale of the QQ questionnaire [39], ranging from 0 (nothing) to 10 (regular quantity).

– Replacement costs associated with employee turnover will be calculated as the sum of the costs for hiring and training a new employee.

#### Process evaluation

A process evaluation will be conducted to evaluate the preparation, implementation, execution, and follow-up of the POSE program according to a number of key components [46,47]. Context (organisational and environmental factors that affect the intervention), recruitment (procedures to recruit employees for the POSE program), and reach (attendance rates of employees) will be evaluated at the level of company management. Information on dose delivered (the amount of program components actually delivered by the providers), dose received (the extent to which employees make use of recommended program components), and fidelity (the extent to which the program was delivered as planned) will be obtained from the OHS. This evaluation will provide deeper insight into components that make the POSE program a failure or a success [48,49]. Furthermore, the satisfaction with the POSE program will be evaluated among participating employees. For that purpose an adapted version of the Client Satisfaction Questionnaire (CSQ-8) [50] and Europep Questionnaire [51] will be sent to all participants nine months after the initiation of the program.

### Sample size

For the sample size calculation, we used the formula proposed by Hussey and Hughes for stepped wedge cluster randomised trials [52]. A pilot study among 116 employees from two plants resulted in a standard deviation (SD) of 7.0 on the WAI and an Intraclass Correlation Coefficient (ICC) for within location clustering of 0.034. Using these figures and assuming a two-sided alpha of 0.05, we calculated that we needed 4 locations with 44 employees each in order to have a 0.90 power to detect a difference of 3 points on the WAI between intervention and CAU. A sensitivity analysis in which we assumed an ICC of 0.10 resulted in four plants with 46 employees each, which is in accordance with the notion that the sample size needed for a stepped wedged trial is relatively insensitive to the ICC [52]. As described under trial design, we will include five plants in the study in order to overcome any potential problems in the inclusion and follow-up of the employees.

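### The stated sample sizes (44 and 46 per plant) do not follow from the stated formula and inputs at 0.90 power; they give about 0.95

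*Protocol article*

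**What the plan says.** The Sample size section of the protocol article names its method, "we used the formula proposed by Hussey and Hughes for stepped wedge cluster randomised trials", and gives every main input: a pilot that "resulted in a standard deviation (SD) of 7.0 on the WAI", an ICC of 0.034, "assuming a two-sided alpha of 0.05", and a target to "detect a difference of 3 points on the WAI between intervention and CAU". The result is "we needed 4 locations with 44 employees each in order to have a 0.90 power". A sensitivity analysis that "assumed an ICC of 0.10 resulted in four plants with 46 employees each" follows. No inflation of either number is mentioned. The reserve against losses is a separate item: "we will include five plants in the study in order to overcome any potential problems in the inclusion and follow-up".

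The Procedure section supplies the layout: a baseline at which no plant has the program, then one plant crossing over at each step.

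**The concern.** The section gives a formula, its inputs and a result, so the result can be checked without any further document. When the inputs are put in, the answers at 0.90 power come out about 9 employees per plant below the stated ones, at both ICC values. This is the only power statement in the protocol. If the sizes and the power do not belong together, one of them is misreported. A reader judging a small or null WAI effect would then take 3 points as the difference the four-plant design can detect with 0.90 power, when it can detect a smaller one.

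**Working it through.** **Inputs.** From Sample size: difference 3, SD 7.0 (variance 49), ICC 0.034 and 0.10, two-sided 0.05, I = 4 plants, power 0.90. From Procedure: one all-control baseline and one plant per step, so four plants give T = 5 waves. The text does not say whether 7.0 is the residual (within-plant) or the total SD, so both were tried.

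**Formula.** With s² = residual variance / n, n employees per plant per wave, and τ² the between-plant variance:

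Var = I·s²·(s² + T·τ²) / [(I·U − W)·s² + (U² + I·T·U − T·W − I·V)·τ²]

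Power = Φ(3/√Var − 1.96)

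U is the number of treated plant-waves, W the sum over waves of squared treated counts, and V the sum over plants of squared treated counts.

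- U = 4+3+2+1 = 10; W = V = 16+9+4+1 = 30.
- I·U − W = 40 − 30 = 10.
- U² + I·T·U − T·W − I·V = 100 + 200 − 150 − 120 = 30.

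**The plan's own figure, 4 x 44 at ICC 0.034.** Take 7.0 as residual SD and τ² = 0.034 x 49 = 1.666.

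- s² = 49/44 = 1.1136.
- Var = 4 x 1.1136 x (1.1136 + 8.33) / (11.136 + 49.98) = 42.07/61.12 = 0.688; SE = 0.830.
- Power = Φ(3/0.830 − 1.96) = Φ(1.656) = 0.951. The stated 0.90 is not reproduced.
- Difference detectable with 0.90 power = (1.960 + 1.282) x 0.830 = 2.69.

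**At 35 per plant, same inputs.** SE = 0.923 and power = 0.902; at 34, power is 0.894. The smallest n for 0.90 is therefore 35.

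**Results, I = 4, T = 5 (ICC 0.034 / ICC 0.10).**

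| Meaning of 7.0 | n for 0.90 | n for 0.95 | Power at 44 / 46 |
|---|---|---|---|
| Residual SD, τ² = ICC x 49 | 35 / 37 | 44 / 46 | 0.951 / 0.950 |
| Residual SD, τ² = ICC/(1−ICC) x 49 | 35 / 37 | 44 / 47 (46.01 unrounded) | 0.951 / 0.950 |
| Total SD | 34 / 34 | 43 / 42 | 0.957 / 0.967 |

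With 7.0 as total SD, the difference detectable with 0.90 power at 4 x 44 is 2.65.

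**Other wave counts at 0.90 power (residual SD).** Four waves need 40 / 44, six need 33 / 34 and seven need 31 / 32. None gives 44 / 46.

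**Unstated adjustments that come close.**

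- A 20% loss allowance: 35/0.8 = 43.75 and 37/0.8 = 46.25.
- A t reference with 10 degrees of freedom at 0.90 power: 43.7 and 45.9, that is 44 and 46 (residual SD).

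**Five plants, six waves, 44 per plant-wave, ICC 0.034.** Here U = 15 and W = V = 55, so the two coefficients are 20 and 70. With residual SD, Var = 0.445, power is 0.994 and the difference detectable with 0.90 power is 2.16. With total SD, power is 0.995 and the difference is 2.13.

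**The case against.** The best defence is that the text names a formula but no reference distribution, and that a condensed article may leave out a loss allowance. A t reference with 10 degrees of freedom, or an allowance of about 20%, would bring the calculation to 44 and 46, or within rounding of them, at the stated 0.90. This stands as far as the cause goes: neither can be excluded. It does not rescue the sentence. The section presents 44 as the number needed "in order to have a 0.90 power to detect a difference of 3 points on the WAI between intervention and CAU" from the listed inputs, and gives the fifth plant as the reserve for inclusion and follow-up problems. If an adjustment was made, the reported inputs are incomplete in a way that changes the result by about a quarter (44 against 35).

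A reader might infer that 0.90 is simply a slip for 0.95, since both stated sizes are the smallest that reach 0.95 in the first row of the table. The documents do not support so firm a diagnosis. The exact match needs 7.0 as residual SD together with τ² = ICC x 49; the standard ICC definition gives 44 and 47, and total SD gives 43 and 42. The text calls 7.0 only a standard deviation.

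A reader might also infer that the trial is at risk. It is not, on this account: the stated sizes deliver more than the promised power, and about 1000 employees are invited against 4 x 44 = 176 required.

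**Conclusion.** The point holds as a reporting error in the power statement. Under the cited formula with its normal test, four plants, one plant per step and five waves, the stated sizes carry power of 0.950 to 0.967 instead of 0.90, and the 0.90 requirement is 34 to 37 per plant instead of 44 to 46. This does not depend on which SD 7.0 is. At ICC 0.034 the difference detectable with 0.90 power is 2.65 to 2.69 points, not 3. The error is on the safe side and touches neither enrolment nor analysis. Its cause cannot be settled from the document. The check takes the formula's own model, which treats measurements in different waves as independent given the plant; whether that suits employees measured repeatedly is a separate question.

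**What to change.** Restate the Sample size section in one of three ways, according to what was done:

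- four plants with 44 (46 at ICC 0.10) employees per plant per wave give power of about 0.95;
- 0.90 power needs 35 (37) per plant per wave, or 34 (34) if 7.0 is the total SD;
- keep 44 and 46 at 0.90, and state the loss allowance or the t reference and its degrees of freedom that produced them.

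In each case, say whether 7.0 is the residual or the total SD and that five waves were assumed. Optionally, add that the five-plant, six-wave design with 44 per plant-wave has power above 0.99 and, at ICC 0.034, detects about 2.13 to 2.16 points with 0.90 power. The cost is a text correction; recruitment, schedule and analysis stay as they are.

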### Blinding

Participants, care providers, and researchers are not blinded for the group assignment.

### Statistical analyses

#### POSE program

The effect of the trial on the primary and secondary outcomes will be analysed using linear (for the continuous outcomes) and logistic (for the binary outcomes) multi-level analyses including a random coefficient for plant and a fixed effect for time. The latter parameter is included to adjust for any potential time effects [52]. All tests will be performed two-sided, assuming an alpha of 0.05.

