### Objective and research questions

The purpose of the FLESH study is to evaluate the effectiveness and cost-benefit of the POSE program on work ability, productivity, and sickness absence among employees in the meat processing industry, compared to care as usual (CAU). The secondary aims are to improve perceived psychosocial and physical workload, health status, and vitality. Along with these evaluations a process evaluation will be conducted among employees and other stakeholders. The objective of this paper is to present the study protocol used in the FLESH study in which the following research questions will be addressed:

1) Does the POSE program improve the primary outcome measures work ability, absenteeism and productivity compared to CAU?

2) Does the POSE program improve the secondary outcome measures psychosocial workload, physical workload, subjective health status and vitality compared to CAU?

3) Is the effectiveness of the POSE program influenced by age, program adherence, risk category, or motivation of management?

4) To what extent do the applied methods appeal to the needs of the involved stakeholders (intervention acceptability)?

5) Is the implementation of the POSE program cost beneficial from the employers’ perspective?

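### Three co-equal primary outcomes are each tested at two-sided 0.05, with no rule for how many must succeed before the program is called effective

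*Protocol article*

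**What the plan says.** Under Outcomes, Effect evaluation, the article states: "The primary outcomes in this study are work ability, productivity and absenteeism". The Abstract lists the same three, and the first research question takes them together: "Does the POSE program improve the primary outcome measures work ability, absenteeism and productivity compared to CAU". None of these places ranks them.

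Under Statistical analyses, POSE program, the multilevel models cover primary and secondary outcomes alike, and the section closes with: "All tests will be performed two-sided, assuming an alpha of 0.05".

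The Sample size section uses the same level: "assuming a two-sided alpha of 0.05, we calculated that we needed 4 locations with 44 employees each". That calculation concerns the WAI alone; its target is 90% power for a 3-point effect.

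The Background calls sustainable employability a multifactorial concept and presents the three outcomes as its usual proxies. The Discussion paragraph of the Abstract and the section on Practical application both speak of the program being shown to be effective, as one conclusion. The article gives no testing order, no adjustment, and no count of primary outcomes that must be significant.

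**The concern.** Three tests that serve three separate claims can each carry 5%. Three tests that serve one claim cannot, unless a rule links them. Here the outcomes are proxies for one concept and the article looks ahead to one conclusion, so the decision rule sets the error rate of that conclusion. Because the rule is missing, a single significant result among the three could be reported as showing the program effective, and 0.05 would not be the error rate of that statement.

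The case is not hypothetical. Under Limitations, the article notes that sickness absence had already fallen from 7.0% to 4.5% and that a further drop may be unrealistic. Mixed results across the three primaries are therefore foreseeable, and the article does not say what they would mean for the overall conclusion. The effect estimates are not biased by this; what is at stake is the strength of the claim drawn from them.

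**Working it through.** **Inputs.** Number of primary outcomes: 3 (Outcomes, Effect evaluation). Level per test: two-sided 0.05 (Statistical analyses). From Sample size: SD 7.0, ICC 0.034 (0.10 in the sensitivity analysis), difference 3 points, power 0.90, four plants of 44 (46 at ICC 0.10), five plants planned.

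**The plan's own sample size.** I used the Hussey-Hughes variance for I plants and T periods, with s² the residual variance of a plant-period mean and τ² the between-plant variance:

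Var = I·s²(s² + Tτ²) / [(IU − W)s² + (U² + ITU − TW − IV)τ²]

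Here U, W and V are the usual sums over the treatment indicators. The article does not state the period count, the SD convention or the reference distribution. I assumed I = 4, T = 5, 44 employees per plant per period, and SD 7 as the residual SD:

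- s² = 49/44 = 1.114; τ² = 49 × 0.034/0.966 = 1.725; U = 10, W = V = 30.
- Var = 4 × 1.114 × (1.114 + 8.623) / (10 × 1.114 + 30 × 1.725) = 0.690, so SE = 0.831 and 3/SE = 3.61.
- With a t reference on IT − I − T = 11 df, power at 44 is 0.91. The smallest n for 0.90 is 43 at ICC 0.034 and 45 at ICC 0.10, against the stated 44 and 46.
- With a normal reference, power at 44 is 0.95 to 0.96 and the required n at ICC 0.034 is only 34 to 35.

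The stated size is thus reproduced to within one employee per plant at an unadjusted 0.05 under the t-based variant.

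**Error rate if any one significant primary counts as success, with no true effect on any of them.**

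- Either direction, independent tests: 1 − 0.95³ = 14.3%.
- Either direction, upper bound under any dependence: 3 × 0.05 = 15%.
- Beneficial direction only, independent tests: 1 − 0.975³ = 7.3%, against 2.5% for one test.

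The documents give no correlation between the outcomes. The range below comes from simulated equicorrelated test statistics:

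| Correlation | Either direction | Benefit only |
|---|---|---|
| 0 | 14.3% | 7.3% |
| 0.2 | 14.0% | 7.0% |
| 0.5 | 12.6% | 6.3% |
| 0.7 | 10.9% | 5.5% |
| 0.9 | 8.3% | 4.2% |

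**Error rate under the other rules.** If all three had to be significant, it would not exceed 5%. If each outcome stood as its own claim, each would carry 5%.

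**Effect of Holm.** The first step is 0.05/3 = 0.0167. With three independent tests, 1 − (1 − 0.0167)³ = 4.9% in either direction.

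- A design with exactly 0.90 power at 0.05 has Φ(1.282 + 1.960 − 2.394) = 0.80 at the first step.
- The four-plant design at 44 each and ICC 0.034 has 0.78 to 0.79 (t) or 0.89 to 0.90 (normal).
- For five plants and six periods at 44 each, under the same residual-SD convention: Var = 5 × 1.114 × (1.114 + 10.348) / (20 × 1.114 + 70 × 1.725) = 0.446, and 3/SE = 4.49. Power at 0.0167 is 0.96 (t, 19 df) or 0.98 (normal). Taking SD 7 as the total SD gives 0.97 and 0.99.
- At ICC 0.10 with 46 each, the five-plant range is again 0.96 to 0.99.

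**The case against.** The strongest reply is that the any-one-of-three rule is nowhere written. The research question joins the outcomes with a plain conjunction, and a multifactorial concept can be reported outcome by outcome. Under an all-three rule or separate claims there is no inflation. This stands as a limit on the figures: they are conditional on one reading. It does not remove the point, because the article leaves that reading open while looking ahead to one conclusion.

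A second reply is that a condensed article may leave multiplicity to the analysis plan. That would answer silence. Here the article fixes 0.05 for all tests, and a later adjustment would contradict that sentence.

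Several stronger readings are tempting and are not supported:

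- **A 14% chance of wrongly calling the program effective.** The 14.3% includes significant worsening, which nobody would report as effectiveness. The figure for false benefit is about 7%. Nor is 14.3% a ceiling; the bound is 15%.
- **Four primary tests, because the QQ has two questions.** The article does not say that the items are tested separately. It does not name a combined score either, which is why one should be named.
- **A power defect for productivity and absenteeism.** The article claims power for the WAI only, so no statement is wrong.
- **The WAI as the only legitimate primary because the trial was sized on it.** The Background puts reduction of sickness absence first among the program's goals. Demoting two declared primaries of a registered trial that started in January 2012 would be a substantive change of outcomes.
- **A hidden adjustment in the sample size.** A normal-based calculation at 0.0167 also lands near 44 (45 to 46 at ICC 0.034), but the text states 0.05.

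**Conclusion.** The point holds, conditionally. Three unranked primary outcomes, a fixed 0.05 for every test and one anticipated conclusion leave the error rate of that conclusion undefined. If one significant primary is enough, the chance of at least one false-positive primary is about 14% in either direction under independence, and the chance of a false claim of benefit is about 7%, nearly three times the nominal 2.5%. Positive correlation lowers both. The stated sample size is not in error on this account. The protocol should be changed, but the issue concerns the decision rule and leaves the effect estimates as they are.

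**What to change.** Keep work ability, productivity and absenteeism as primary. Name in advance the single QQ score that represents productivity. For the primary outcomes, replace the alpha sentence under Statistical analyses with: the three are tested by Holm's procedure at family-wise two-sided 0.05 (smallest p-value against 0.0167, the next against 0.025, the last against 0.05), and any overall claim of effectiveness rests on the Holm-adjusted results and names the outcomes that support it. Record this as a dated amendment before outcome data are compared between conditions.

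Holm needs no assumption about the correlation between outcomes and leaves the declared primaries unchanged. Its cost is some power: at the first step a design with exactly 0.90 drops to about 0.80. With the planned five plants, WAI power for 3 points stays at about 0.96 to 0.99 even at 44 employees per plant, under the period and SD assumptions shown in the working. No extra recruitment or measurement is needed.

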#### Cost-benefit

The effect of the trial on the costs will also be analyzed using linear multi-level analyses including a random coefficient for plant and a fixed effect for time. Bootstrapping will be used in case the costs will turn out to follow a positively skewed distribution.

## Discussion

This paper presents the design of a stepped wedge trial to evaluate the effectiveness of a comprehensive workers’ health surveillance program in a meat production environment. The POSE program aims to balance the functional capacities of employees with work demands. Detecting and restoring imbalances between capacities and demands in an early stage may contribute to sustained employability.

The current state of WHS programs and the use of FCEs in employment examinations have recently been reviewed [20,21]. The authors observed no evidence for an association between the length of FCEs and injury relapse. They also observed that general health examinations did not lead to decreased sickness absence, but did lead to more rejected job applications. Furthermore, they observed that job-specific pre-employment examinations lead to reduced occupational disease, injury or sickness absence. The effectiveness of pre-employment examinations, including FCE, on musculoskeletal injuries could not be demonstrated. On the other hand, several individual studies have demonstrated the predictive value of FCE on sustainable return to work [53], risk for future work disability [54] and claim closure / benefit suspension [55,56]. Better FCE performance was associated with better outcomes, i.e. earlier return to work, lower risk for future work disability and earlier claim closure. In the above mentioned studies WHS and FCE results were used in association with work outcomes, not as a screener to deploy tailor-made interventions. No studies were identified reporting on WHS, FCE and integrated interventions, which underpins the need for this study.

